### **Exclusion Criteria:**

1. Comorbid psychiatric disorder other than anxiety or depression, such as psychotic disorder, obsessive compulsive disorder, eating disorders (i.e., anorexia and bulimia), bipolar disorder; developmental or organic mental disorders; and current (past 6 months) substance use disorders and current post-traumatic stress disorder as assessed by clinician at screening visit
2. A serious medical condition that may result in surgery or hospitalization.
3. A history of head trauma causing prolonged loss of consciousness, or ongoing cognitive impairment
4. Inability to understand study procedures or informed consent process, or significant personality dysfunction likely to interfere with study participation (assessed during the clinical interview).
5. Subjects who will be non-compliant with the study procedures. This may include planned travel out of town.
6. Pregnancy as assessed by urine test at screen. Avoidance of pregnancy is also necessary for inclusion in this study.
7. Subjects taking barbiturates, SSRIs, anti-depressants, or antipsychotics. Sleep medications (other than anti-depressants) and benzodiazepines will be allowed, if has been taken at stable dose 4 weeks prior to baseline and the patient plans to continue at the same dose through the trial. Trazadone (for sleep) above 100mg will be disallowed.

8. Concurrent psychotherapy initiated within 1 month of screen interview, or ongoing psychotherapy of any duration directed specifically toward the treatment of anxiety (such as Cognitive Behavioral Therapy).
9. Individuals who have completed a course of MBSR or an equivalent meditation training in the last year, or have an ongoing daily meditation practice.
10. Individuals reporting significant active suicidal ideation or suicidal behaviors within the past year.
11. Individuals with a medical condition (i.e., epilepsy) that may be exacerbated by study treatment, as determined by a study physician or nurse practitioner based on history, physical, and/or labs.

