## **VI. SUBJECT ENROLLMENT**

All participants will be recruited from the general public to participate in a study investigating the effects of MBSR compared to escitalopram on anxiety disorders. Most participants are expected to be self-referred, treatment-seeking patients. In addition, patients will be recruited through: 1) word of mouth referrals, 2) referrals from area medical and mental health professionals at the three sites, 3) Patient partner-panel and IRB approved information about the study on our websites and through local approved postings, and 4) advertisements placed in local media. Potential participants who contact the research assistant will be screened for eligibility and interest in research participation. If interested and eligible for the study, they will meet with the study clinician who will obtain written informed consent after a thorough explanation of procedures including the treatment options along with a brief rationale for these approaches, and the potential risks involved in participation. The participant will be invited to ask questions which will be answered. Patients will be asked to sign the informed consent statement. The consent form will also state that participation is voluntary, that participants can refuse to answer any question, that they can withdraw from the study at any time, and that study participation in no way affects their care at GUMC, MGH, or NYU. The IRBs of GUMC, MGH, and NYU will have approved the protocol and consent forms prior to the initiation of the study. If the participant signs the consent form, they will be given a copy of the consent form regardless of whether they enroll in the study.

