## **VII. STUDY PROCEDURES**

Patients with anxiety disorders from nearby communities and in the surrounding metropolitan areas will be invited to participate through study recruitment materials. Participants may be engaged using IRB-approved print and radio advertisements and clinic referral at GUMC, NYU, and MGH. Participants may also be solicited through IRB-approved media, flyers, postings and other primary care and psychiatric clinic facilities and programs. Referrals may be made by medical and mental health practitioners in the area as well as self-referrals by affected individuals.

Individuals who contact the study coordinators at each site will be phone screened for general medical and diagnostic treatment eligibility and interest in research participation. If they are eligible and interested, they will then have a meeting with a study clinician to evaluate their psychiatric diagnosis and eligibility. This first visit (Screening Visit) includes a psychiatric (using the MINI interview) and medical assessment and brief physical exam, to determine eligibility. The study clinician will inquire whether the participant has a primary care clinician or psychiatrist who already did a medical work up to rule out medical causes of anxiety symptoms. If they have, staff will ask the participant to sign a release form in order to give permission to speak with the participant's doctor or to provide the study team with a copy of past blood tests or ECG

or if neither a confirmation from records or the outside provider is not possible, study staff will perform an ECG and blood test.

For all participants, urine testing for pregnancy and drugs of abuse will be completed to help determine whether exclusion criteria are met (pregnancy, substance abuse) by the research coordinator. The Screening Visit will take about 3 hours. The study will be open to adults 18 – 75 years old who have an anxiety disorder; all races, and ethnicities and genders are invited. We will repeat the Screening Visit if extenuating circumstances lead to an abnormally long waiting time between the Screening Visit and Baseline Visit, in order to obtain the most accurate and up-to-date information.

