#### Escitalopram (ESC)

During the 8 weeks of randomized treatment with ESC, subjects will be seen at baseline, post-baseline medication pick-up visit, weeks 1, 2, 4, 6, and 8 week endpoint, and at 12 week follow-up, (9 visits total) by a study physician/nurse practitioner. Georgetown University Medical Center's research pharmacy will be responsible for preparing the medication, which will be given to the participants by a study M.D. from baseline to week 12. Patients will take the pills each day at home. ESC will be initiated at 10 mg/day; which will be continued to week 2, when it will be increased to 20mg/day if well tolerated (or delayed if not). Medication adherence will be assessed by pill count and a standardized adherence measurement [68]. Side effects will be assessed at each visit and recorded. Participants will also be instructed to contact study staff immediately if any significant side effects, symptomatic worsening, or suicidal ideation develops in between visits. After week 12, if the patient desires to stay on the medication, s/he will be given a prescription by the study MD/NP., who will also start the process of transition to outpatient care so that the patient can continue treatment after the end of the study, if desired.

If in-person visits are not possible for any reason (e.g., coronavirus), the study medication will be shipped directly to the patient from the research pharmacy following the pharmacy protocols and the study visits will be conducted using telehealth videoconferencing or telephone contact.

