In addition, there is a risk of increased suicidality with initiation of SSRI's in people with depression age 24 and under: subjects in this protocol will receive close monitoring for the development of suicidality (see Procedures to Minimize Risk in section 9.3). Escitalopram may also cause unexpected side effects. Adverse events (side effects) will be assessed by the study clinician. Participants will be instructed to contact the study physician/nurse practitioner should any adverse events or concerning side effects occur; if appropriate, the study doctor will refer him/her to treatment. At present there is insufficient information regarding the safety of escitalopram during pregnancy or breastfeeding. The procedures used in this study may be unsafe for an unborn baby. If you, as a subject of study, are a woman of child bearing potential, you must agree to avoid pregnancy during your participation in this study.

For more information about risks, contact the principal investigator at [contact].

If you do become pregnant during the study, you should immediately notify [name] at [contact]. In addition, if you are already pregnant, you cannot participate in this study. There are risks to suddenly stopping escitalopram including flu-like symptoms, headaches, and paresthesias. These can be uncomfortable but are not dangerous.

(vi) Blood draw (for screening labs):

When blood is drawn, patients may feel some pain and have some bruising and/or bleeding at the needle site. Occasionally, a person feels faint when blood is drawn. Rarely, an infection, which can be treated, may develop at the injection site.

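### The protocol flags escitalopram safety as insufficiently known in breastfeeding, but no written criterion or screening step keeps a breastfeeding participant from being randomised to it

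*Protocol*

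**What the plan says.** Section IX (Risks and Discomforts), under escitalopram, states: "At present there is insufficient information regarding the safety of escitalopram during pregnancy or breastfeeding". It then adds, for pregnancy only, "The procedures used in this study may be unsafe for an unborn baby". Women of child-bearing potential must agree to avoid pregnancy, and the reader is told that "if you are already pregnant, you cannot participate in this study".

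The rules that decide entry are in section V. Exclusion 6 reads: "Pregnancy as assessed by urine test at screen. Avoidance of pregnancy is also necessary for inclusion in this study". The nearest general clause is exclusion 11, which begins "Individuals with a medical condition (i.e., epilepsy) that may be exacerbated by study treatment" and leaves the decision to a study physician or nurse practitioner.

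Section VII (Study Procedures) says that "urine testing for pregnancy and drugs of abuse will be completed to help determine whether exclusion criteria are met", and the Table of Assessments lists a urine pregnancy and drug test at screening. Section VI (Subject Enrollment) requires the clinician to explain, before consent, "the potential risks involved in participation".

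Section VII, Escitalopram (ESC), describes the study medication, "which will be given to the participants by a study M.D. from baseline to week 12". The dose starts at 10 mg/day and rises to 20 mg/day at week 2 if tolerated.

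**The concern.** The protocol names two states in which it considers the drug's safety insufficiently known, and then writes entry rules for one of them. Pregnancy has an exclusion, a test, a duty of avoidance and an explicit bar. Breastfeeding has none of these.

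What is at stake is participant and infant safety. A site can comply fully with the protocol and still supply escitalopram to a breastfeeding woman, and the exposure could extend to an infant who has given no consent. With three sites and no written rule, the decision would rest on local judgement and could differ between sites. This is a gap in eligibility, not a contradiction between two statements, and it has no bearing on the non-inferiority comparison.

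**Working it through.** The protocol gives no figure of its own on this point, so the check is mainly a comparison of texts.

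**Step 1. Set each rule beside the risk statement.**

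| Place in the Protocol | Pregnancy | Breastfeeding |
|---|---|---|
| IX, statement on insufficient safety information | named | named |
| V, exclusion 6 | excluded, and must be avoided | not named |
| VII, urine test at the Screening Visit | tested | not named |
| Table of Assessments, screening column | tested | not named |
| IX, duty on women of child-bearing potential | must avoid | not named |
| IX, who cannot participate | barred | not named |

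**Step 2. Check whether another criterion covers it.**

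- Exclusion 11 concerns a medical condition of the participant that treatment may worsen. Breastfeeding is not such a condition, and the worry is the infant's exposure, not worsening of the mother's health.
- Inclusion 3 requires willingness to accept the assigned treatment. It removes a woman who would refuse the drug. It does not remove an informed woman who accepts either arm.
- Inclusion 1 admits women from age 18, so breastfeeding women can be in the eligible population. A urine pregnancy test does not detect breastfeeding.

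**Step 3. Exposure, given one breastfeeding entrant.**

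- Allocation is 1:1 (section VIII, Outcome Assessment): 368 / 2 = 184 planned per arm, so P(escitalopram) = 184 / 368 = 0.5. This only restates the allocation ratio.
- Study supply from baseline to week 12: 12 × 7 = 84 days at most.
- At 10 mg/day to week 2: 2 × 7 = 14 days.
- At 20 mg/day from week 2 to week 12, if titrated on schedule: 10 × 7 = 70 days at most.

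**Step 4. What cannot be computed.** The documents give no proportion of breastfeeding women among candidates, so no expected number exposed is given. They also contain nothing from which to quantify the risk to an infant.

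**The case against.** The strongest reply has four parts.

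- **The risk section grades its two statements differently.** Information is called insufficient for both states, but only the unborn baby is said to be possibly at risk from the study procedures. On this reading the pregnancy rules follow the stronger statement, and disclosing the breastfeeding risk while leaving the choice to clinician and participant is a legitimate preference. This partly explains why the pregnancy rules are stricter. It does not explain why nothing at all is written for breastfeeding. Disclosure informs the mother but does not decide eligibility.
- **Screening is wider than a urine test.** The phone screen covers general medical eligibility, and the Screening Visit includes a medical assessment and physical exam whose items are not listed. A clinician may well ask about breastfeeding and decline to enrol. That is possible, but no written criterion tells the clinician what to do with the answer.
- **The consent pages are not in the reviewed text.** They could carry an instruction on breastfeeding. This stands as a limit on the claim, which covers only the written criteria and procedures.
- **The size is unknown.** Ages run from 18 to 75 and both sexes are eligible, so very few participants, or none, may be affected. This stands too, and it is why no number is claimed.

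These points narrow the concern, but none of them supplies a written rule.

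**Conclusion.** The concern holds. As written, the eligibility criteria and screening procedures permit randomisation of a breastfeeding participant to a drug whose safety in that state the same protocol calls insufficiently known. For one such entrant the probability of assignment to escitalopram is 0.5, followed by up to 84 days of study-supplied drug, of which up to 70 days are at 20 mg/day. The durations are maxima and assume full adherence and titration on schedule.

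The conclusion does not claim that escitalopram is contraindicated or harmful in breastfeeding; the protocol says only that information is insufficient. It also does not claim that the unseen consent or screening forms are silent. The validity of the trial is not threatened, but the gap should be closed.

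**What to change.** 1. Extend exclusion 6 to current breastfeeding, or intent to breastfeed during the study drug period.
2. Add a question on breastfeeding to the Screening Visit in section VII, asked before randomisation.
3. In section IX, name breastfeeding beside pregnancy in the statement on who cannot participate.

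The cost is one phrase in exclusion 6, one phrase in section IX and one screening question. Some otherwise eligible women would be excluded. Their number is not given in the documents and is assumed to be small. The sample size and the analysis do not change.

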## **VI. SUBJECT ENROLLMENT**

All participants will be recruited from the general public to participate in a study investigating the effects of MBSR compared to escitalopram on anxiety disorders. Most participants are expected to be self-referred, treatment-seeking patients. In addition, patients will be recruited through: 1) word of mouth referrals, 2) referrals from area medical and mental health professionals at the three sites, 3) Patient partner-panel and IRB approved information about the study on our websites and through local approved postings, and 4) advertisements placed in local media. Potential participants who contact the research assistant will be screened for eligibility and interest in research participation. If interested and eligible for the study, they will meet with the study clinician who will obtain written informed consent after a thorough explanation of procedures including the treatment options along with a brief rationale for these approaches, and the potential risks involved in participation. The participant will be invited to ask questions which will be answered. Patients will be asked to sign the informed consent statement. The consent form will also state that participation is voluntary, that participants can refuse to answer any question, that they can withdraw from the study at any time, and that study participation in no way affects their care at GUMC, MGH, or NYU. The IRBs of GUMC, MGH, and NYU will have approved the protocol and consent forms prior to the initiation of the study. If the participant signs the consent form, they will be given a copy of the consent form regardless of whether they enroll in the study.

## **VII. STUDY PROCEDURES**

Patients with anxiety disorders from nearby communities and in the surrounding metropolitan areas will be invited to participate through study recruitment materials. Participants may be engaged using IRB-approved print and radio advertisements and clinic referral at GUMC, NYU, and MGH. Participants may also be solicited through IRB-approved media, flyers, postings and other primary care and psychiatric clinic facilities and programs. Referrals may be made by medical and mental health practitioners in the area as well as self-referrals by affected individuals.

Individuals who contact the study coordinators at each site will be phone screened for general medical and diagnostic treatment eligibility and interest in research participation. If they are eligible and interested, they will then have a meeting with a study clinician to evaluate their psychiatric diagnosis and eligibility. This first visit (Screening Visit) includes a psychiatric (using the MINI interview) and medical assessment and brief physical exam, to determine eligibility. The study clinician will inquire whether the participant has a primary care clinician or psychiatrist who already did a medical work up to rule out medical causes of anxiety symptoms. If they have, staff will ask the participant to sign a release form in order to give permission to speak with the participant's doctor or to provide the study team with a copy of past blood tests or ECG

or if neither a confirmation from records or the outside provider is not possible, study staff will perform an ECG and blood test.

For all participants, urine testing for pregnancy and drugs of abuse will be completed to help determine whether exclusion criteria are met (pregnancy, substance abuse) by the research coordinator. The Screening Visit will take about 3 hours. The study will be open to adults 18 – 75 years old who have an anxiety disorder; all races, and ethnicities and genders are invited. We will repeat the Screening Visit if extenuating circumstances lead to an abnormally long waiting time between the Screening Visit and Baseline Visit, in order to obtain the most accurate and up-to-date information.

The second study visit in the Baseline Assessment visit, which takes place within the 6-week period before the start of treatment. If unusual circumstances prevent the participant from beginning treatment within the 6-week window following the Baseline Assessment, the visit will be repeated to obtain the most accurate and up-to-date information. Patients will be assessed by the “Independent Evaluator” who will remain blind to treatment allocation, and who will complete the clinician-rated instruments (please see Table of Assessments). Assessments will be made by trained, independent evaluators (IE's) either in person, by videoconferencing, or by phone. If assessments are completed by videoconferencing or phone due to concerns of coronavirus, we will omit collecting vital signs and weight at that visit. All IEs for this multicenter trial will be undergoing shared training and supervision across sites. If necessary, IE's can assess patients at any of the study sites. Patients will be asked to complete a series of patient-reported questionnaires (please see table that consist of questions about the participants' thoughts, feelings, anxiety symptoms, depression symptoms, adverse and traumatic experiences in the past, sleep, and other topics; these will be repeated in subsequent study visits (see Table of Assessments).

#### Table of Assessments

| Study Week                                                      | Screen | Baseline Assessment visit | Week 1 | Week 2 | Week 4 | Week 6 | Primary Endpoint visit | Follow-up: Week 12 | Follow-Up: Week 24 |
|-----------------------------------------------------------------|--------|---------------------------|--------|--------|--------|--------|------------------------|--------------------|--------------------|
| Patient-reported measures of outcome                            |        |                           |        |        |        |        |                        |                    |                    |
| Demographics                                                    | ✖      |                           |        |        |        |        |                        |                    |                    |
| Anxiety (OASIS anxiety scale)                                   |        | ✖                         | ✖      | ✖      | ✖      | ✖      | ✖                      | ✖                  | ✖                  |
| Anxiety (BAI)                                                   |        | ✖                         |        |        | ✖      |        | ✖                      | ✖                  | ✖                  |
| Worry (PSWQ)                                                    |        | ✖                         |        |        | ✖      |        | ✖                      | ✖                  | ✖                  |
| Emotion Regulation (DERS-SF)                                    |        | ✖                         |        |        | ✖      |        | ✖                      |                    |                    |
| Self-Compassion Scale (SCS)                                     |        | ✖                         |        |        | ✖      |        | ✖                      |                    |                    |
| Emotional distress (PROMIS-Depression SF and PROMIS-Anxiety SF) |        | ✖                         |        |        | ✖      |        | ✖                      | ✖                  | ✖                  |
| Treatment Satisfaction (CSQ, RTQ)                               |        |                           | ✖      |        | ✖      |        | ✖                      | ✖                  |                    |
| Sleep ( PSQI, PROMIS-sleep anxiety measure )                    |        | ✖                         |        |        | ✖      |        | ✖                      |                    | ✖                  |
| Quality of Life/Functioning                                     |        | ✖                         |        |        | ✖      |        | ✖                      | ✖                  | ✖                  |

|                                                          |   |    |   |   |   |   |   |   |   |
|----------------------------------------------------------|---|----|---|---|---|---|---|---|---|
| (PROMIS- SPSR and PROMIS- APSRA-8)                       |   |    |   |   |   |   |   |   |   |
| Adverse Experiences (CTQ and LEC)                        | ✖ |    |   |   |   |   |   |   |   |
| Work performance (HPQ)                                   |   | ✖  |   |   |   |   |   |   | ✖ |
| Clinician-rated assessments of outcome                   |   |    |   |   |   |   |   |   |   |
| Psychiatric Diagnoses (MINI)                             | ✖ |    |   |   |   |   |   |   |   |
| Anxiety symptom severity (CGI-S /CGI-I)                  |   | ✖  |   |   | ✖ |   | ✖ | ✖ | ✖ |
| Disorder-specific scales (PDSS, SIGH-A, LSAS)            |   | ✖  |   |   | ✖ |   | ✖ | ✖ | ✖ |
| Measures of Safety and Study Integrity                   |   |    |   |   |   |   |   |   |   |
| Side Effects (FIBSER & Adverse Events)                   |   |    | ✖ | ✖ | ✖ | ✖ | ✖ | ✖ | ✖ |
| Adherence/ Homework                                      |   |    | ✖ | ✖ | ✖ | ✖ | ✖ | ✖ | ✖ |
| Depressive symptoms (QIDS-SR including suicidality item) |   | ✖  |   |   | ✖ |   | ✖ | ✖ |   |
| Vital Signs                                              | ✖ |    |   |   | ✖ |   | ✖ |   |   |
| Clinician Suicide Assessment                             | ✖ | ✖* | ✖ | ✖ | ✖ | ✖ | ✖ | ✖ | ✖ |
| Concomitant Treatment                                    | ✖ | ✖* | ✖ | ✖ | ✖ | ✖ | ✖ | ✖ | ✖ |
| Weight                                                   | ✖ |    |   |   | ✖ |   | ✖ |   |   |
| Blood draw, ECG, Urine pregnancy/drug test**             | ✖ |    |   |   |   |   |   |   |   |

\*these measures will be repeated with MD/NP during first week of treatment (referred to as “week 0”) unless the participant has been randomized to MBSR *and* less than two weeks elapse between that participant’s baseline visit and the start of their treatment)

\*\*these procedures will only be completed if pre-existing records are not obtainable

Participants will be paid a total of \$160 participation in the study. If a patient misses a treatment visit, the provider (MBSR instructor or Medical Rater) will reach out to them and work with the patient to minimize any barriers. For all assessment visits, including the follow-up visits at 12 and 24 weeks, we will offer flexible visits which can be done over the phone, videoconferencing, and/or electronically, if needed. In order to reduce missing data, as well as reducing the likelihood that treatment related dropout biases the available data for this effectiveness study in which treatment satisfaction, tolerability, adherence and response are all clinically relevant, to the extent feasible, we will follow subjects who miss treatment visits or drop out of the assigned protocol (either voluntarily, or removed by the study due to adverse effects) and continue to collect their assessment data and include them in the analysis according to their original assignment.

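### The Table of Assessments footnote makes the screening urine pregnancy and drug tests conditional on missing records, against the procedures text and exclusion criterion 6

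*Protocol*

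**What the plan says.** Three places in the protocol govern the screening urine tests.

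- **Table of Assessments (section VII).** A single row reads "Blood draw, ECG, Urine pregnancy/drug test". It is marked at the Screen visit only and carries a double asterisk. The footnote to that marker says "these procedures will only be completed if pre-existing records are not obtainable".
- **Section VII, Study Procedures, text on the Screening Visit.** Staff ask whether an outside clinician has already ruled out medical causes of the anxiety. If so, they seek permission to speak with that clinician or "to provide the study team with a copy of past blood tests or ECG". The fallback is "or if neither a confirmation from records or the outside provider is not possible, study staff will perform an ECG and blood test". The next paragraph says "For all participants, urine testing for pregnancy and drugs of abuse will be completed to help determine whether exclusion criteria are met".
- **Section V, Exclusion Criteria.** Criterion 6 reads "Pregnancy as assessed by urine test at screen". Criterion 1 covers current "substance use disorders and current post-traumatic stress disorder as assessed by clinician at screening visit".

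On the reason for testing, section IX (Risks and Discomforts) says "At present there is insufficient information regarding the safety of escitalopram during pregnancy or breastfeeding".

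**The concern.** The schedule and the text give different rules for the same test. Under the text, every participant has a urine pregnancy and drug test at screening. Under the footnote, the test is done only when earlier records cannot be had. Staff often work from the schedule table, and the trial runs at three sites, so two sites could screen differently and each point to the protocol.

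Pregnancy is an exclusion, half of those randomised are assigned to escitalopram, and the protocol itself regards the drug's safety in pregnancy as not established. The error therefore runs in the unsafe direction. A site that followed the footnote would also fail criterion 6 as written, which is an eligibility deviation produced by the protocol's own table.

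**Working it through.** No arithmetic applies. The check is whether any reading of the row and footnote agrees with the other two statements.

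**1. What the marker covers.** There are two possibilities.
- It covers the whole row. Then blood draw, ECG and urine test all depend on records being unobtainable.
- It covers only the item it follows. That item is the urine test, so the urine test is conditional and the blood draw and ECG are not.

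The urine test is conditional either way.

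**2. What the records exception covers in the text.** Section VII asks for past blood tests or an ECG, and the fallback names an ECG and a blood test. Urine results appear in neither. The separate sentence on urine testing applies to all participants and mentions no exception for records. Text and footnote therefore disagree on the urine test and on nothing else in the row, if the marker is taken to cover the whole row.

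**3. Whether an old record could satisfy the exclusion.** Criterion 6 ties the pregnancy exclusion to a urine test at screening. A result obtained elsewhere at an earlier date is not that test. The footnote sets no limit on the age of a record. Reusing an earlier ECG or blood work-up is reasonable for the stated purpose of ruling out medical causes of anxiety. An earlier negative pregnancy test says nothing about pregnancy now.

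**4. Whether a later visit would catch the omission.** The row is marked at Screen and nowhere else. The single-asterisk footnote repeats some assessments in the first week of treatment, but it is attached to the suicide assessment and concomitant treatment rows. The schedule therefore has no second pregnancy test before dosing.

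**5. Which exclusions depend on the test.**

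| Exclusion | How the protocol assesses it | Effect of skipping the urine test |
|---|---|---|
| Pregnancy (criterion 6) | Urine test at screening | The named assessment is missing |
| Current substance use disorder (criterion 1) | Clinician at the screening visit, with the urine test as support | Supporting evidence is lost; the named assessment remains |

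The direct conflict with a criterion is the pregnancy one. For substance use, the conflict is with the procedures text only.

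**The case against.** The best defence is that the intent is plain. Section VII confines the records exception to the ECG and blood test and then requires urine testing of everyone, and criterion 6 names the test. Two specific statements stand against one general footnote on a merged row, and a site would have to overlook both to randomise an untested participant. The footnote can also be read test by test: a procedure is waived only if a record of that same procedure exists. The protocol never asks outside providers for urine results, so few people would be exempt. Criterion 6 also requires avoidance of pregnancy, section IX requires immediate notification if pregnancy occurs, and only the escitalopram arm is exposed to the drug during randomised treatment.

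Much of this stands as a limit on reach. The marker was probably meant for the blood draw and ECG alone, the affected group may be small, and the substance-use side is weaker because that exclusion rests on clinician assessment. None of it removes the contradiction. Nothing in the protocol says that the text prevails over the table. Even on the test-by-test reading, an earlier urine result would excuse a participant from a test that the text requires of all and that criterion 6 places at screening. Avoiding pregnancy and reporting it later do not replace a test before the first dose.

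**Conclusion.** The concern holds. The footnote makes the screening urine tests conditional on missing records, and this conflicts with the procedures text and, for pregnancy, with exclusion criterion 6. The conflict appears on either reading of what the marker covers.

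Its size cannot be given. The protocol does not state what share of participants have obtainable outside records, or what share of those records include urine results. If any outside record waives the whole row, everyone with obtainable records is affected, which could be few or most of those randomised. If each test needs its own record, only those with an earlier urine result are affected, and the protocol has no process for seeking such results. The safety consequence is confined to participants who could be pregnant and, for drug exposure during randomised treatment, to those assigned to escitalopram.

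This is an inconsistency in eligibility and safety procedures. It has no bearing on the primary endpoint, the non-inferiority margin, the sample size or the analysis. It should be corrected because it concerns a safety exclusion and the correction is small.

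**What to change.** Split the table row in two:

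- Blood draw and ECG, at Screen, with the double-asterisk footnote kept.
- Urine pregnancy/drug test, at Screen, with no footnote.

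Reword the footnote to name the blood draw and ECG, so that it cannot be read more widely. The schedule, section VII and criterion 6 then state one rule.

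The cost is one table edit and one footnote edit. At most, some participants have a screening urine test that a literal reading of the footnote would have spared them, and section VII already requires that test of everyone.
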